### Statistical analysis

2.12

Initial descriptive analyses will be used to evaluate baseline comparability among the three intervention groups, using ANOVA or Kruskal-Wallis tests for continuous variables and chi-square tests for categorical variables. We will conduct an intention-to-treat analysis for our primary and secondary endpoints. Specifically, we will conduct a t-test for the primary endpoint of difference in change in minutes of exercise for the SUP and UNSUP exercise group relative to control. The SUP and UNSUP exercise intervention will be compared to control separately. The 95% confidence interval for the mean of the difference in change in minutes of exercise will be reported. Statistical testing is for exploratory purpose, without multiple testing adjustment.

Post-intervention outcomes, including cardiovascular risk factors, patient-reported outcomes, and physical function, at 8-months will be evaluated using generalized linear mixed effects model with random intercept to adjust for clustering of repeated measurements within participants. If the primary analyses shows statistical significance, then a sensitivity analysis with multiple imputation of missing data will be conducted to test the robustness of the results. If judged to be MAR or MCAR multiple imputation will be used and between imputation variability incorporated using Rubin’s rule. We will use generalized linear mixed effects models for analyses of continuous outcomes, with appropriate distribution and link selected for any that are not normally distributed. Distribution of primary and secondary endpoints will also be examined by key socio-demographic factors (e.g. income, education level, employment status, and zip code) to explore whether these socio-demographic factors are associated with the endpoints of interest. Statistical testing will be conducted at a family-wise two-sided α = 0.05 level to determine statistical significance. All analyses will be performed using SAS (version 9.4, SAS Institute, Cary, NC).

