### Randomization and blinding

2.4

After baseline assessments are completed, patients are randomly assigned to the SUP, UNSUP, or AC group with an equal allocation ratio (1:1:1) using block randomization with a block size of 6. The randomization is stratified by cancer stage (i.e., I, II, III for breast cancer, and I, II, III, or metastatic for prostate and colorectal cancer) which is assessed at time of diagnosis. A study biostatistician ([name]) creates the randomization schema before the trial begins, and the randomization allocation is given to staff through a web-based application (REDCap) (35). The study investigators are blind to the randomization process. The intervention allocation is not hidden from the study participants, interventionists, and outcome assessors due to the nature of exercise intervention.

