### Sample size

2.11

In order to assess change from baseline to post-intervention in daily exercise minutes for the SUP intervention versus AC; and the UNSUP intervention vs. AC, we anticipate to enroll a total of 45 patients with breast, prostate, or colorectal cancers, who will be randomized to SUP (n=15) or UNSUP (n=15) exercise groups, or AC (n=15). Based on data from a recent study led by Lee et al. (2019) examining how a HIIT intervention was feasible for breast cancer patients undergoing chemotherapy, we assume the average weekly minutes of moderate-to-vigorous physical activity to be 30 minutes for all participants at baseline, 60 minutes for the SUP and UNSUP exercise groups and 45 minutes for the AC during 4-month post-intervention, with standard deviation of 12. To detect such difference in the pre-post change in mean minutes of exercise per week (corresponding to a standardized effect size of 1.25), comparing supervised and unsupervised exercise groups to control group using t-test, with two-sided α = 0.05, a sample size of 12 subjects in each group is needed in order to achieve 80% power. Assuming 80% drop off between baseline and post-intervention (Week 17-19), a sample size of 15 patients each group is needed to be randomized.

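### The primary test is an unadjusted t-test on change, and the SD of 12 behind its 80% power is not identified as an SD of level or of change; a three-arm baseline-adjusted ANCOVA removes the dependence

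*Protocol article*

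**What the plan says.** Section 2.12 (Statistical analysis) sets the primary test: "we will conduct a t-test for the primary endpoint of difference in change in minutes of exercise". SUP and UNSUP are each compared with AC separately, a 95% confidence interval is reported, and neither baseline activity nor cancer stage enters the test.

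Section 2.11 (Sample size) supplies the assumptions. At baseline, "we assume the average weekly minutes of moderate-to-vigorous physical activity to be 30 minutes for all participants at baseline". After the intervention the means are 60 in both exercise arms and "45 minutes for the AC during 4-month post-intervention, with standard deviation of 12". The difference in pre-post change is then described as "corresponding to a standardized effect size of 1.25". The calculation is made "using t-test, with two-sided α = 0.05", and concludes that "a sample size of 12 subjects in each group is needed in order to achieve 80% power"; 15 per arm are to be randomized.

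Section 2.4 (Randomization and blinding) states: "The randomization is stratified by cancer stage". Sections 2.6 and 2.6.1 show that accelerometer minutes are measured at Week 0 and Week 17, so the baseline value is available for analysis.

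**The concern.** The SD of 12 directly follows a list of mean weekly minutes, so it reads most naturally as the spread of weekly minutes between patients. The effect size of 1.25 treats the same number as the spread of within-patient change. The two are equal only under a particular relation between baseline and Week 17, and the article states none.

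The choice of test makes this matter. A change score carries the noise of both measurements, so its power depends strongly on r. Low values of r are plausible here, though not demonstrated. Entry is limited to 60 minutes or less of structured exercise a week, which tends to narrow the baseline range. Chemotherapy starts around baseline, and about 17 weeks separate the two measurements. At stake are the power that justifies 45 patients and the width of the confidence intervals meant to inform larger trials.

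**Working it through.** **Inputs from section 2.11.** Change in the exercise arms 60 − 30 = 30; change in AC 45 − 30 = 15; difference 15 minutes a week. SD 12. Two-sided α 0.05. Evaluable n = 12 per arm. The correlation r is not given, so it is varied below.

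**The plan's own figure.** 15/12 = 1.25. A two-sample t-test (noncentral t) at effect size 1.25 has power 0.796 with 11 per arm and 0.833 with 12. Twelve is therefore the smallest n that reaches 80%, and the stated figure reproduces if 12 is the SD of change. 12/0.8 = 15 randomized.

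**If 12 is the SD of weekly minutes at both visits (assumption).**

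- Planned test: SD of change = 12·√(2(1 − r)).
- ANCOVA: residual SD = 12·√(1 − r²).

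Power with 12 per arm (ANCOVA: two-arm model, baseline only, 21 df):

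| r | SD of change | t-test on change | ANCOVA residual SD | ANCOVA |
|---|---|---|---|---|
| 0 | 17.0 | 54% | 12.0 | 83% |
| 0.3 | 14.2 | 70% | 11.4 | 86% |
| 0.4 | 13.1 | 76% | 11.0 | 89% |
| 0.5 | 12.0 | 83% | 10.4 | 92% |

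The t-test crosses 80% between r = 0.45 (79.7%) and r = 0.46 (80.4%). At r = 0.3 it needs 16 evaluable per arm, against 11 for ANCOVA. At r = 0.3 the 95% CI half-width is 2.074 × 14.20 × √(2/12) = 12.0 minutes for the t-test. For a three-arm ANCOVA (32 df) it is 2.037 × 11.45 × √(2/12) = 9.5 minutes.

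**If 12 is the SD of change (equal SDs at the two visits).** The ANCOVA residual SD is 12·√((1 + r)/2): 8.5 at r = 0 and 11.1 at r = 0.7. Power runs from 98% down to 89%, against 83% for the t-test at every r.

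**Why ANCOVA does not lose.** With equal SDs of 12, Var(change) = 144·2(1 − r) and the ANCOVA residual variance is 144(1 − r²). They differ by 144(1 − r)², which is never negative. For r of 0 or above, the ANCOVA residual SD is at most 12 under both readings.

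**Check by simulation.** The formula leaves out the small cost of chance baseline imbalance. Simulated power for baseline-only ANCOVA at r = 0, 0.3 and 0.5:

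- two-arm models: about 80–81%, 84–85% and 90–91%;
- one three-arm model: about 82–84%, 86–87% and 91–93%.

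**Adding stage.** Stage alone has four levels (I, II, III, metastatic). Crossed with cancer type as section 2.4 lists them, there are 3 + 4 + 4 = 11 cells. With stage given no prognostic value, simulated power at r = 0, 0.3 and 0.5 was:

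- four levels, one three-arm model: about 79–81%, 83–84% and 89–91%;
- four levels, pairwise models: about 74–77%, 79–81% and 85–88%;
- 11 cells, one three-arm model: about 68–72%, 72–78% and 79–84%;
- 11 cells, pairwise models: about 56–65%, 60–69% and 69–77%.

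The ranges span simulations that differed in how arms and stages were allocated.

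**The case against.** A reader might infer that the trial is underpowered or that the 80% is wrong. The article does not support that. The SD is never labelled, and the sentence that uses it refers to pre-post change. On that reading the stated sample size is exact. The source of the figures is a cited study that is not at hand.

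The threshold near r = 0.46 also assumes the same SD at both visits. Suppose instead that the Week 17 SD is 12 and the baseline SD is 6, 8 or 10, which the entry limit on exercise makes credible. At r = 0.3 the SD of change is then √(144 + s² − 7.2s) = 11.7, 12.3 or 13.1, and the t-test has 85%, 82% or 76% power instead of 70%. A larger baseline SD would move it the other way. This objection stands, and it is why the power is called unsupported and not false.

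A second tempting inference is that adjusting for baseline and stage together guarantees the power at no cost. That is true of baseline only. Stage uses degrees of freedom, and fine levels can take power below 80%. Stage with real prognostic value would recover some of that loss, but the article gives no figure for it.

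Third, a t-test on change is unbiased under randomization, it matches the test used for the sample size, and section 2.12 calls the testing exploratory. All true, so validity is not in question. But section 2.11 still justifies 45 patients by 80% power, and exploratory intervals benefit from precision as much as confirmatory ones do. Nor is the test a detail left to an unseen analysis plan: the article names it.

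**Conclusion.** The point holds as a matter of efficiency and of an unstated assumption. The primary test leaves out a baseline value that is already collected. Its 80% power rests on an SD whose meaning is not given and, if that SD describes weekly minutes with equal spread at both visits, on an unstated correlation of at least about 0.46. Under that reading power ranges from 54% at r = 0 to 83% at r = 0.5; if 12 is the SD of change it is 83%. Baseline-adjusted ANCOVA gives about 80% or more across r of 0 and above under either reading, so the change is worth making whichever is meant. This rests on the article's own difference of 15 minutes, 12 evaluable patients per arm, roughly normal outcomes, and a Week 17 SD no larger than the readings above imply.

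**What to change.** In section 2.12, replace the separate t-tests with one three-arm ANCOVA of Week 17 weekly moderate-to-vigorous minutes on arm and baseline minutes. Report the SUP−AC and UNSUP−AC differences with 95% confidence intervals from that model.

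If stage is to be included, fix a coarse grouping in advance (for example metastatic versus not) within the same three-arm model. Do not use separate pairwise models or the 11 type-by-stage cells, and do not leave the grouping to be chosen after the data are seen.

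In section 2.11, state whether 12 is the SD of weekly minutes or of change, give the assumed correlation (and both visit SDs if they differ), and restate the power for the analysis actually planned.

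The cost is rewording of two sections and one degree of freedom for baseline. A coarse stage term costs little more, whereas four non-prognostic levels cost a few points of power (to about 79% at r = 0). No additional patients, visits or measurements are needed.

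### Section 2.12 states both that there is no multiplicity adjustment and that testing is at a family-wise 0.05; the two planned primary t-tests have a family-wise error of about 9%, so the second statement is false for this plan

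*Protocol article*

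**What the plan says.** Section 2.12 (Statistical analysis) of the protocol article sets the primary analysis as a t-test on change in minutes of exercise: "we will conduct a t-test for the primary endpoint of difference in change in minutes of exercise for the SUP and UNSUP exercise group". It adds that "The SUP and UNSUP exercise intervention will be compared to control separately", which makes two primary comparisons with one control arm. The paragraph describing these tests and their 95% confidence interval closes with "Statistical testing is for exploratory purpose, without multiple testing adjustment".

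The next paragraph covers the mixed models, missing data and socio-demographic summaries. Towards its end it says: "Statistical testing will be conducted at a family-wise two-sided α = 0.05 level to determine statistical significance". It does not define the family or name a procedure that would control the error rate over it.

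Section 2.11 (Sample size) sizes each comparison as a single test: "comparing supervised and unsupervised exercise groups to control group using t-test, with two-sided α = 0.05".

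**The concern.** A family-wise level is a statement about the chance of any false positive across a set of tests. Unadjusted testing of two hypotheses at 0.05 each does not hold that chance at 0.05. The two sentences share the same unrestricted subject, statistical testing in general, so the text gives no ground for applying one to the primary endpoint and the other only to the secondary outcomes.

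Two things are at stake. First, a reader who relies on the last sentence will believe that the chance of at least one false primary finding is 5%, when the tests as described carry nearly twice that. Second, some results would be called significant under one sentence and not under the other, and with both in print the choice could be made after the p-values are seen. The call also has a consequence inside the plan, because section 2.12 makes the multiple-imputation sensitivity analysis conditional on a significant primary result.

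**Working it through.** **Inputs.** All come from sections 2.11 and 2.12: two comparisons with a shared control; 1:1:1 allocation; two-sided 0.05; 12 evaluable and 15 randomized per group; 60 against 45 minutes with SD 12.

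**Step 1: reproduce the plan's sample size.** The assumptions are "60 minutes for the SUP and UNSUP exercise groups and 45 minutes for the AC during 4-month post-intervention, with standard deviation of 12", with the same baseline of 30 minutes in all arms.
- Difference in change: (60 − 30) − (45 − 30) = 15 minutes.
- Standardized effect: 15 / 12 = 1.25, as stated ("corresponding to a standardized effect size of 1.25").
- Noncentrality at n = 12: 1.25 × √(12/2) = 3.06, on 22 df.
- At two-sided 0.05 the critical value is 2.07 and exact power is 83.3%. At n = 11 it is 79.6%.

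So 12 per group is the smallest number that reaches 80% with an unadjusted 0.05 per comparison. The stated figure is reproduced.

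**Step 2: the same calculation at a Bonferroni level.** With 0.025 per comparison the critical value at n = 12 is 2.41.

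| Evaluable per group | Power at 0.05 | Power at 0.025 |
|---|---|---|
| 12 | 83.3% | 74.0% |
| 13 | 86.4% | 78.1% |
| 14 | 88.9% | 81.7% |
| 15 | 91.0% | 84.8% |

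A Bonferroni split would need 14 evaluable per group for 80%. The plan's 12 does not come from that level.

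**Step 3: family-wise error of the two tests as planned.**
- Upper bound: 0.05 + 0.05 = 10%.
- If the tests were independent: 1 − 0.95² = 9.75%.
- With a shared control and equal arms the two statistics have correlation 0.5. Then 1 − P(|Z₁| < 1.96 and |Z₂| < 1.96) = 9.07%.
- Simulation of two t-tests sharing a control arm (300,000 to 400,000 replicates): 9.0% to 9.1% at n = 12 and at n = 15.

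**Step 4: what control at a family-wise 0.05 would do to power** (n = 12, effect 1.25, per comparison).

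| Rule | Power per comparison |
|---|---|
| Unadjusted 0.05 | 83% |
| Holm, both effects real | 80% |
| Holm, one effect real | 74% |
| Dunnett (critical value 2.31 on 33 df) | 77% |
| Bonferroni | 74% |

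**Step 5: how often the rule changes a verdict.** These are the simulated trials at n = 12 in which unadjusted testing and Holm disagree on at least one primary comparison:
- both effects at the design value: 6.0%
- only one effect real: just under 10%
- no effect in either arm: 4.4%

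**The case against.** The strongest reply is that the authors' intention is clear enough. The sentence on no adjustment stands beside the primary tests. The sample size fits only that reading. The family-wise sentence comes later, names no procedure, and may be one stray word. Unadjusted comparison of two distinct interventions in a 45-patient trial labelled exploratory is a legitimate choice, and the Discussion describes the results as preliminary and meant to inform later trials.

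Most of this stands, and it limits the point in three ways.

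- A reader might infer that the trial has no primary decision rule at all. The documents do not support that: two places agree on an unadjusted 0.05 per comparison, so the rule is contradicted rather than absent.
- A reader might infer that the 9% is an error in itself. It is one only when set against the family-wise sentence; under a declared unadjusted plan it is an accepted property that should be disclosed.
- A reader might infer that every p-value between 0.025 and 0.05 changes verdict. That is so under Bonferroni. Under Holm such a result is still significant when the other comparison has p ≤ 0.025.

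What the reply does not remove is the sentence itself. It covers all statistical testing, it claims a property that the planned tests lack, and limiting it to secondary outcomes would not help because no procedure is named for those either. Nor is this detail left to an unseen analysis plan: such a plan could follow only one of the two statements.

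**Conclusion.** The contradiction holds. As described, the two primary tests have a family-wise error of about 9.1%, against the 5% that the last sentence claims. The figure assumes equal arms, a shared control, a common SD and no true effect in either arm; it hardly depends on whether 12 or 15 per arm are analysed.

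The sizing is not broken. It is consistent with unadjusted testing, and under the plan's own assumption that both exercise arms reach 60 minutes, Holm at 12 per group would still give about 80%. The practical reach is moderate: under the planning assumptions the choice between unadjusted testing and Holm alters at least one primary verdict in about 6% of trials, and estimates and intervals are reported either way. It is nevertheless the primary significance rule, so it should be settled before analysis.

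**What to change.** Choose one rule before any comparison of outcomes by arm.

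**(a) Unadjusted.** Delete the family-wise wording. State two-sided 0.05 for each primary comparison with unadjusted 95% confidence intervals, and disclose that the chance of at least one false positive across the two comparisons is about 9%. Section 2.11 stays as it is and no power is lost. The cost is that no claim of family-wise control can be made.

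**(b) Controlled.** Keep family-wise 0.05 for the two primary comparisons only and name the procedure, for example Holm or Dunnett. Remove the exploratory, no-adjustment wording for the primary endpoint; otherwise a confirmatory rule would sit beside a disclaimer. Make the reported intervals match the rule, since an unadjusted 95% interval can exclude zero where the procedure does not reject. Restate power in section 2.11 at 12 evaluable per group: Holm about 80% if both effects are real and 74% if only one is; Dunnett about 77%. The cost is 3 to 9 percentage points of power per comparison relative to 83%.

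Under either option, label the secondary outcomes exploratory, report them with unadjusted 95% intervals, and make no family-wise claim for them. Both options change only text and need no additional patients, unless the sponsor wants to hold 80% power under Dunnett, or under Holm when only one effect is real.

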#### Primary outcomes

2.6.1

Minutes of moderate-to-vigorous physical activity are utilized as the primary outcome variable and assessed via the ActiGraph wGT3X-BT (*ActiGraph, Pensacola, FL*), which is worn by patients for seven days at all times except for water activities and sleeping. Other measures of physical activity such as sedentary time, light physical activity, step count etc. are also captured using the ActiGraph. Additionally, the 7-day Physical Activity Recall interview is conducted over the phone asking participants to recall their exercise for the same 7 days that the ActiGraph was worn. Only wake wear time is utilized, and participants must have recorded a minimum of four days with at least 600 minutes of wake wear time per day for inclusion in the analysis. Non-wear time is excluded from the analysis, defined as≥90minutes of consecutive zeros with a 2-minute spike tolerance (39). Commonly used cutoff points among cancer patients will be used to classify sedentary time (<100 counts per minute), light physical activity (100–1951 counts per minute), and moderate-to-vigorous physical activity (≥1952 counts per minute) (40, 41).

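### The imputation check on the primary t-test runs only after a significant result, so a non-significant result affected by dropout is never examined

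*Protocol article*

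**What the plan says.** Section 2.12 (Statistical analysis) states the principle: "We will conduct an intention-to-treat analysis for our primary and secondary endpoints". It then makes this specific for the primary endpoint: "we will conduct a t-test for the primary endpoint of difference in change in minutes of exercise", with each exercise arm compared with control separately. It does not say how a missing value is handled within that test.

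Missing data appear in two sentences of the same section. The first is "If the primary analyses shows statistical significance, then a sensitivity analysis with multiple imputation of missing data will be conducted". The second begins "If judged to be MAR or MCAR multiple imputation will be used" and adds that variances are combined by Rubin's rule.

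Two other sections determine who can be in the test. Section 2.6.1 (Primary outcomes) sets a wear-time rule: "participants must have recorded a minimum of four days with at least 600 minutes of wake wear time per day for inclusion in the analysis". Section 2.11 (Sample size) says "with two-sided α = 0.05, a sample size of 12 subjects in each group is needed in order to achieve 80% power" and randomises 15 per group to allow for losses before the post-intervention visit.

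**The concern.** A t-test on change needs a value at both visits. Imputation is reserved for the sensitivity step, so the primary test is an observed-case analysis in all but name. That is common and can be defended, provided the effect of the missing patients is then examined.

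Here the examination depends on the result. Loss of patients can move the estimate either way. If it inflates the difference and the test is significant, imputation follows. If it shrinks the difference and the test is not significant, nothing follows. The robustness statement is then available for positive results only.

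The second condition has its own difficulty. The observed data cannot distinguish MAR from MNAR, and the section names no analysis for data judged MNAR. Imputation under MAR also takes the MAR assumption as given, so it cannot show how far the conclusion depends on it.

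The article says its results will guide larger trials. A non-significant pilot estimate needs this check as much as a significant one.

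**Working it through.** **1. The plan's own figure.** Section 2.11 assumes 30 min/week at baseline in all arms, then "60 minutes for the SUP and UNSUP exercise groups and 45 minutes for the AC during 4-month post-intervention, with standard deviation of 12". The difference in change is (60 - 30) - (45 - 30) = 15, and 15/12 = 1.25, which matches "corresponding to a standardized effect size of 1.25". By the noncentral t distribution, two-sided alpha 0.05, power is 79.6% with 11 per group and 83.3% with 12. So 12 is the smallest size reaching 80%, and the plan's figure is reproduced.

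**2. Expected number missing.** 12/(1 - 0.20) = 15 matches the plan. 12/(1 - 0.80) = 60 does not. The stated 80% drop-off is therefore read as 80% retention, which is an inference. On that reading 3 of 15 per arm, or 9 of 45, are expected to be absent from the primary test.

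**3. Bias from missing patients.** With a fraction m missing in one arm, bias in that arm's observed mean = m × (mean change of observed patients - mean change of missing patients). With m = 0.20, each 10 min/week gap gives 2 min/week of bias, in either direction.

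**4. Illustration of the unexamined case (assumed missingness).** The true difference is 15 and the SD of change is 12. The exercise arm loses the 3 of 15 patients who are highest on a latent variable with correlation r to change. The control arm loses 3 at random.

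The expected mean of the top 3 of 15 standard normal values is 1.311, so the retained 12 average -(3 × 1.311)/12 = -0.328. Bias = r × 12 × (-0.328):
- r = 0.5: -1.97
- r = 0.7: -2.75

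Simulation of the two-sample t-test (100,000 trials per setting) gives:

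| r | Bias (min/week) | Power | Non-significant, so no imputation |
|---|---|---|---|
| 0 | 0.0 | 83% | 17% |
| 0.3 | -1.2 | 78% | 22% |
| 0.5 | -2.0 | 74% | 26% |
| 0.7 | -2.7 | 71% | 29% |

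About 17% of trials would be non-significant even with random loss. The excess due to informative loss is therefore about 10 to 13 percentage points.

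**5. The same mechanism in both arms.** Bias is 0.0 at every r, and power is not reduced.

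**The case against.** The strongest case against is that this is a condensed article, that testing is described as exploratory, and that the clause governs a secondary check. It does not change the primary estimate, its confidence interval or the sample size. That stands and limits the severity. It does not remove the point: the significance trigger is a stated rule, and an analysis plan that ran imputation regardless would contradict it.

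Two sentences might be read as rescue. Section 2.12 also plans mixed models for continuous outcomes, but it specifically assigns the primary endpoint a t-test. The MAR/MCAR sentence might be meant as unconditional, but it would then conflict with the sentence before it.

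Three stronger readings are tempting and not supported.
- **That the plan abandons intention-to-treat.** Nothing departs from analysis by randomised group. The 70% adherence threshold in section 2.7 classifies compliance and is not an exclusion. Section 2.8 follows all patients unless consent is withdrawn. The wear-time rule concerns measurement validity. Observed-case analysis is an inference from the text, though a sound one.
- **That this clause inflates type I error to 7% to 9%.** With no true effect and informative loss in the exercise arm only, rejection is about 7% (r = 0.5) to 9% (r = 0.7). With the same loss in both arms, bias is zero and rejection is about 6% to 7%. No section supports arm-specific informative loss. Those false positives are also significant results, after which the plan would run imputation.
- **That the t-test must be replaced.** Patients with only a baseline value add little information about change. Assuming a pre-post correlation of 0.5, a likelihood model using all baselines still leaves about three quarters of the bias (1.5 against 1.9 at r = 0.5; 2.1 against 2.8 at r = 0.7).

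**Conclusion.** The point holds in this form: as written, a non-significant primary result receives no missing-data analysis, and the one analysis provided cannot address departure from MAR. The asymmetry follows from the text and needs no simulation.

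Its size does rest on assumptions: 20% loss, SD 12, and loss of larger-gain patients in the exercise arm only. On those, the estimate is reduced by about 13% (2.0/15) to 18% (2.7/15) of the planned effect, and roughly one trial in four or slightly more ends non-significant and unexamined. With similar loss in both arms the bias is nil. Nothing in the documents says which pattern is likely.

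This should be fixed before the data are analysed. It is not critical, because testing is stated to be exploratory.

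**What to change.** In section 2.12, or in the analysis plan with a matching correction:
1. Delete the condition that the primary result be significant and the condition that data be judged MAR or MCAR.
2. Run multiple imputation whatever the primary p-value, by randomised arm, using auxiliary data already collected: the 7-day recall (2.6.1), adherence (2.7) and symptom scores (2.6.2.7). The session and phone-call symptom checklist is described for the two exercise arms only, so the control-arm model must rely on the measures taken at visits and on stretching and activity records.
3. Add a delta-adjusted version that shifts the imputed values over a stated range in both directions, to show what departure from MAR would change the conclusion.
4. Describe the t-test population as randomised patients, in their assigned arm, with valid accelerometry at both visits, and report the number and reasons missing per arm.

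The t-test may stay primary; a likelihood-based repeated-measures model is optional. The cost is wording and a few hours of extra analysis. The sample size and data collection do not change.
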